## Abstract

**Introduction:**

Congenital ectopia lentis (CEL) is a rare ocular disease characterised by the dislocation or displacement of the lens. Patients with mild lens dislocations can be treated with conservative methods (eg, corrective eyeglasses or contact lenses). In contrast, patients with severe CEL usually require surgical management. However, few studies have focused on the visual prognosis and complications in conservative and surgical management of patients. This study aims to investigate the prognosis and complications in patients with CEL with conservative and surgical management, which is vital for CEL management, especially the choice of surgical timing and surgical method.

**Methods and analysis:**

A cohort study will be conducted at Zhongshan Ophthalmic Center. We plan to recruit 604 participants diagnosed with CEL and aged ≥3 years old. Patients with mild lens subluxation and stable visual conditions will be included in the non-surgical group and follow-up at 1, 2 and 3 years after enrolment. Patients with severe lens subluxation who accept CEL surgery will be included in the surgical group. Different surgical techniques, including phacoemulsification, in-the-bag intraocular lens implantation (with or without capsular tension ring) and trans-scleral fixation, will be used depending on the severity of dislocation. Patients will be followed up at 3 months, and 1, 2 and 3 years postoperatively. Over a 5-year follow-up period, patients will receive a detailed ocular examination, including optometry, biological measurement, specular microscopy, ultrasound biomicroscopy, anterior segment and posterior segment optical coherence tomography (OCT), OCT angiography, echocardiography and questionnaires on vision-related quality of life. The primary outcome is the change of best-corrected visual acuity and the incidence of complications in both groups.

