### Preoperative management

All patients diagnosed with CEL will be followed up since the enrolment. The surgery will be performed when either of the following situations occurs: (1) BCVA <0.3 in LogMAR acuity; (2) monocular diplopia; (3) progressive subluxation of the lens affecting the pupillary axis; (4) complicated with severe cataract or secondary glaucoma or corneal endothelial decompensation or retinal detachment.^8^

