### Outcome measures

#### Primary outcome

The primary outcome is the change of BCVA and the incidence of complications (time frame: non-surgical group is evaluated at the first visit and 1, 2, 3 years after enrolment; surgical group is evaluated at preoperation, 3 months, and 1, 2, 3 years postoperatively).

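### Leaving the non-surgical group depends partly on the primary outcomes, and the stated groups, baselines and tests do not handle patients who convert to surgery

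*Protocol article*

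**What the plan says.** All references are to the protocol article.

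- **Groups (abstract, Methods and analysis).** "Patients with mild lens subluxation and stable visual conditions will be included in the non-surgical group". For the other group: "Patients with severe lens subluxation who accept CEL surgery will be included in the surgical group".
- **Movement between groups (Preoperative management).** "All patients diagnosed with CEL will be followed up since the enrolment". Surgery follows when any one of four situations occurs. The first three are "1) BCVA <0.3 in LogMAR acuity; (2) monocular diplopia; (3) progressive subluxation of the lens affecting the pupillary axis". The fourth is "complicated with severe cataract or secondary glaucoma or corneal endothelial decompensation or retinal detachment".
- **Outcome and time origin (Primary outcome).** "The primary outcome is the change of BCVA and the incidence of complications". The "non-surgical group is evaluated at the first visit and 1, 2, 3 years after enrolment". The surgical group is assessed before the operation, at 3 months, and at 1, 2 and 3 years after it.
- **Analysis (Statistical analysis plan).** Proportions are compared between groups by chi-square or Fisher's exact test. Differences in BCVA change are given with 95% CIs, followed by linear regression.
- **Data capture (Examinations).** Adverse events and complications are collected at each visit.

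**The concern.** The objective is the prognosis under conservative and surgical management, as a guide to when to operate. That requires knowing how often, when and why conservative management ends. Under this design a patient can start conservatively, cross a BCVA threshold or develop a severe complication, and then be operated on. The event that ends the conservative period is then itself a primary-outcome observation.

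The article does not say whether that event counts as a conservative-phase complication, whether the BCVA at the decision visit enters the non-surgical change, or which group the patient belongs to afterwards. The surgical baseline is preoperative, so the worsened state can become the starting point from which surgical change is measured. If the non-surgical results rest on those still unoperated at years 1, 2 and 3, that group has been selected on the outcome being reported.

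**Working it through.** **Step 1. Triggers against primary outcomes.**

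| Surgery trigger | Part of the primary outcome? |
|---|---|
| 1. BCVA threshold | Yes, BCVA change |
| 2. Monocular diplopia | Not named |
| 3. Progressive subluxation affecting the pupillary axis | Not named (disease progression) |
| 4. Severe cataract, secondary glaucoma, endothelial decompensation, retinal detachment | Yes, complications |

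The overlap is two of four. BCVA loss short of the threshold and complications outside item 4 are outcomes that do not trigger surgery.

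**Step 2. The protocol's own figure.** The Sample size section assumes 15% complications with a relative margin of 20%, so E = 0.15 × 0.20 = 0.03. Then n = 1.96² × 0.15 × 0.85 / 0.03² = 544.2, and 544 / 0.9 = 604.4. The stated 544 and 604 reproduce (the printed denominator omits the square, but 544 follows only with it). This is the only outcome rate in the document. It refers to CEL patients in general and is borrowed below for the conservative phase.

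**Step 3. Complication incidence among stayers.** Let I = 0.15 be the 3-year incidence and q the share of patients with a complication whose complication triggers surgery (assumed). If these patients leave both numerator and denominator, and nobody leaves for another reason, incidence among stayers = I(1 − q) / (1 − Iq).

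| q | Calculation | Stayers | If the event is counted before the switch |
|---|---|---|---|
| 0 | 0.15 / 1 | 15.0% | 15% |
| 0.25 | 0.1125 / 0.9625 | 11.7% | 15% |
| 0.50 | 0.075 / 0.925 | 8.1% | 15% |
| 0.75 | 0.0375 / 0.8875 | 4.2% | 15% |
| 1 | 0 / 0.85 | 0% | 15% |

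**Step 4. BCVA change.** The trigger is an absolute level, so the illustration uses a level and not an amount of change. All inputs are assumed: yearly drift 0, 0.02 or 0.05 LogMAR, yearly SD 0.05 or 0.08, measurement error SD 0.04, and conversion at the first annual visit at which the trigger is met. On LogMAR a higher value is worse vision.

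- *Reading A:* conversion at LogMAR 0.3 or worse; baseline mean 0.15, SD 0.08, restricted to below 0.3.
- *Reading B:* the rule as printed, conversion below LogMAR 0.3; baseline mean 0.45, SD 0.08, restricted to 0.3 or above.

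Each range runs from yearly SD 0.05 to 0.08.

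| True 3-year change | Stayers, A | Converted, A | Stayers, B | Converted, B |
|---|---|---|---|---|
| 0.00 | −0.014 to −0.042 | 15.0% to 24.0% | 0.014 to 0.042 | 15.0% to 23.8% |
| 0.06 | 0.035 to 0.000 | 27.3% to 35.2% | 0.068 to 0.088 | 7.3% to 15.2% |
| 0.15 | 0.101 to 0.054 | 53.1% to 55.0% | 0.152 to 0.163 | 2.2% to 7.0% |

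Under A stayers look better than the whole cohort; under B they look slightly worse. Under A, merely keeping the year-3 value of patients who first cross at year 3 moves the middle row to 0.047 to 0.025, which is closer to 0.06.

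**Step 5. Which reading?** The Introduction cites one recommendation to operate when near vision is worse than 0.4 LogMAR, and another when BCVA is less than 0.3 with no scale given. Preoperative management attaches LogMAR to the less-than-0.3 rule. These two sections must be reconciled before the direction of a BCVA bias can be stated.

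**The case against.** The strongest reply is that stable vision is naturally read as an entry criterion, that complications are recorded at every visit, and that the article nowhere says events before conversion are discarded. If the triggering event is counted when it is seen, incidence is not understated. The flow chart and the supplementary visit table are not shown and may settle the matter, and competing-risk methods are usual content for a separate analysis plan.

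Much of this stands, and it rules out three stronger readings that a reader might infer:

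- *That patients leave exactly when a primary outcome event occurs.* Only two of the four triggers are primary outcomes, many outcome events trigger nothing, and surgery also needs the patient's acceptance.
- *That the result is biased towards no harm, in a known direction.* For complications this holds only if trigger events are left out of the conservative results. For BCVA the direction reverses with the reading of the threshold.
- *That the plan removes the failures.* It does not say so. It leaves the way open.

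It is also fair that outcomes are named per group and that the sample size serves one overall proportion, so the problem bears first on the conservative estimate and only then on any contrast between groups.

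The reply does not remove the point. Group labels, two different time origins and simple tests are stated in the article itself. Followed as written, they give converters no defined place in the non-surgical results and give them a reset baseline in the surgical ones.

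**Conclusion.** The concern holds in a conditional form. Exit from the non-surgical group depends partly on the primary outcomes, and the stated structure and tests do not handle it, so results from patients still unoperated at years 1, 2 and 3 are open to selection on outcome.

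For complications, the conservative-phase incidence is understated if trigger events are not counted there: about 8.1% against 15% when half of complications trigger surgery, and anywhere from 15% to 0% as that share runs from none to all. A figure of 7.5% (0.15 × 0.5) would apply only if the events were deleted while the patients stayed in the denominator. For BCVA neither direction nor size can be fixed from the documents, which give no conversion rate, no BCVA standard deviation and an unresolved threshold. The BCVA figures above are illustrations only.

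**What to change.** 1. Classify patients by management at enrolment, with stable vision as an entry criterion only and not a condition on later course.
2. Count a trigger event as a complication of the conservative phase, and keep converters' decision-visit BCVA in the conservative results, labelled as change up to conversion.
3. Report the 3-year cumulative incidence of complications from enrolment, with surgery for other reasons as a competing event, and the cumulative incidence of conversion to surgery by reason.
4. Enter converters' postoperative data in the surgical cohort from the day of surgery.
5. Keep and report complications found at the 3-month postoperative visit, and note the unequal visit schedule in any between-group comparison. Restricting incidence to the shared yearly visits looks tidy but could hide early surgical complications.
6. Reconcile the BCVA threshold wording in the Introduction and Preoperative management.

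The cost is a few sentences of definition and some extra analysis of data already collected. The conservative results are likely to look less favourable than those of patients who never converted.

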**Ethics and dissemination:**

Ethics approval was obtained from the ethics committee of the Zhongshan Ophthalmic Center (number: 2022KYPJ207). Study findings will be published in a peer-reviewed journal.

**Trial registration number:**

NCT05654025.

STRENGTHS AND LIMITATIONS OF THIS STUDYThis study is a cohort of congenital ectopia lentis (CEL) in the Chinese population with a relatively large sample size and a comparatively long (5 years) follow-up.This study assesses important ophthalmic measurements with significant clinical implications, including visual acuity, intraocular pressure, axial length, high-order aberrations, choroidal thickness and choriocapillaris flow deficits.Important systemic indicators of Marfan syndrome are measured, including the metacarpophalangeal joint length, incidence of valvular heart disease, aortic root diameter and Z-score.In this study, CEL in age less than 3 years old is excluded and participants could be lost to follow-up after surgery.This study focuses on individuals with CEL, but different subtypes of CEL may not be classified.

## Introduction

Congenital ectopia lentis (CEL) is a rare ocular disease characterised by the dislocation or displacement of the lens. Several systemic diseases have been reported to be associated with CEL, such as Marfan syndrome, homocystinuria, Weill-Marchesani syndrome and Ehlers-Danlos syndrome.^1^ However, some patients with CEL may have no known systemic manifestations.^2^

Patients with mild lens dislocations can be treated with conservative methods (eg, corrective eyeglasses or contact lenses).^3^ However, progressive subluxation or complete dislocation of the lens can cause a high degree of myopia or astigmatism, even amblyopia.^4^ Surgical intervention is crucial in the management of patients with severe CEL.^5^ Currently, there is no unified standard for operation timing for CEL. A previous study recommended surgical intervention when the near vision of children was worse than 0.4 in LogMAR acuity.^6^ However, some researchers suggested that surgery should be performed when the best-corrected visual acuity (BCVA) is less than 0.3 or monocular diplopia occurs.^4 7^ Few studies have focused on the refractive change and visual prognosis in patients with CEL both with conservative management and surgical management.^8^

Several surgical techniques have been reported over the past decades, such as lensectomy, phacoemulsification without intraocular lens (IOL) implantation, phacoemulsification and IOL implantation (with or without capsular tension ring) and various trans-scleral fixations of IOL.^9–11^ However, the safety and efficacy of these techniques have not been fully validated so far, especially in the Chinese population. Herein, we will conduct this cohort study at the Zhongshan Ophthalmic Center, one of the biggest ophthalmic hospitals in China.^12^ All children diagnosed with CEL will be followed up for at least 3 years. Long-term changes in BCVA and the incidence of complications will be evaluated in patients with conservative and surgical management.

## Methods and analysis

This study will be conducted from 5 December 2022 to 5 December 2027. The study was registered on ClinicalTrials.gov (NCT05654025).

### Objective

The study is designed as a prospective clinical trial to investigate the prognosis and complications in patients with CEL with conservative and surgical management. The aim is to serve as a reference for disease management, specifically for choice of surgical timing and surgical method.

### Study design

An approximately 5-year cohort study will be conducted at Zhongshan Ophthalmic Center, Guangzhou, China. This study will adhere to the Declaration of Helsinki, and ethics have been approved by the ethics committee of the Zhongshan Ophthalmic Center (number: 2022KYPJ207). This study is designed used the Standard Protocol Items: Recommendations for Interventional Trials reporting guidelines.^13^

### Eligibility criteria

#### Inclusion criteria

Diagnosed with congenital lens dislocation and age ≥3 years old.Agree to participate in this study with written informed consent from patients or legal guardians.

#### Exclusion criteria

History of ophthalmic trauma or other ophthalmic surgeries.Combined with other ophthalmic diseases such as primary glaucoma, uveitis and corneal disease.Patients who could not cooperate in the examinations.

### Study setting and participants

This cohort study will be conducted at Zhongshan Ophthalmic Center, one of the largest ophthalmic hospitals in China. This study aims to investigate the visual prognosis and complications in patients with CEL with different kinds of management. Patients aged 3 years or above diagnosed with CEL will be recruited from Zhongshan Ophthalmic Center. Moreover, each participant will be followed for at least 3 years.

Once the participants meet the requirement of our eligibility criteria, they will be asked to join the WeChat (an instant messaging tool) group on the phone and be provided with informed consent. Interested participants or their guardians will sign the consent form and, if appropriate, will complete a thorough ocular examination and systemic evaluations.

### Recruitment

The outpatient clinics will carry out the first screening at Zhongshan Ophthalmic Center. Potential participants will be further confirmed by eligibility and recruited at Zhongshan Ophthalmic Center for clinical trials. One of our researchers will contact the participants and explain the trial process in detail to ensure the participants or guardians fully understand the whole study. Once they agree and sign the consent form, further information will be provided, including the purpose of the study, examinations, the importance of follow-up time and duration, and possible risk in treatment. Then, the trial will proceed subsequently.

### Sample size

Sample size will be estimated as follows: assuming the incidence of complications in patients with CEL is 15%, and the margin of error is 20%. For a 5% significance level, Z_α/2_ is 1.96 for the two-tailed alternative hypothesis. Sample size=(Z_α/2_)^2^×P(1−P)×1/E^2^=(1.96)^2^×15%×(1–15%)/(15%×20%)=544. Assuming the loss ratio of 10%, the adjusted sample size will be 544/(1–0.1)=544/0.9=604.

### Preoperative management

All patients diagnosed with CEL will be followed up since the enrolment. The surgery will be performed when either of the following situations occurs: (1) BCVA <0.3 in LogMAR acuity; (2) monocular diplopia; (3) progressive subluxation of the lens affecting the pupillary axis; (4) complicated with severe cataract or secondary glaucoma or corneal endothelial decompensation or retinal detachment.^8^

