
### Examinations

Baseline data and follow-up examination items are as follows:

Demographic characteristics, including name, gender and date of birth.Slit-lamp examination: slit-lamp examination (BQ-900, Haag Streit, Switzerland) and fundus examination will be performed at each visit.Visual acuity and refraction: the uncorrected visual acuity and BCVA will be evaluated with Early Treatment of Diabetic Retinopathy Study (ETDRS) LogMAR visual acuity chart (Precision Vision, Villa Park, Illinois, USA) at a test distance of 4.0 m. The refractive error will be determined by subjective refraction following an objective measurement. Spherical equivalent will be obtained with the calculation of spherical power plus half of the cylindrical power.Axial length measures: axial length will be measured using IOLMaster 700 (Carl Zeiss, Jena, Germany).High-order aberrations will be assessed using Nidek OPD-Scan III (Gamagori, Japan).Corneal endothelial cell counting and morphology will be detected using an endokeratoscope (SP-2000P, Topcon, Japan).The state of zonules will be assessed clock by clock with ultrasound biomicroscopy. The clock range of zonular disruption or loosening will be recorded. These results will be confirmed using slit-lamp photography after dilation.The structure of the anterior chamber angle will be examined using a Tomey Casia 2 anterior segment optical coherence tomography (OCT) (Tomey, Tokyo, Japan).^16^
The tilt and eccentricity of IOL will be evaluated using Pentacam AXL (Oculus, Germany).^17^

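### Acuity criterion for surgery is inverted or on the wrong scale: as written, BCVA below 0.3 LogMAR selects eyes better than about 20/40

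*Protocol article*

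**What the plan says.** The Preoperative management section lists four situations that lead to surgery and opens: "The surgery will be performed when either of the following situations occurs: (1) BCVA <0.3 in LogMAR acuity". The other three are monocular diplopia, progressive subluxation that reaches the pupillary axis, and serious complications such as severe cataract or retinal detachment. The list is worded as alternatives, so the first item is sufficient alone.

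The Examinations section fixes the scale: "the uncorrected visual acuity and BCVA will be evaluated with Early Treatment of Diabetic Retinopathy Study (ETDRS) LogMAR visual acuity chart", at 4.0 m.

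The abstract (Methods and analysis) describes the two groups. "Patients with mild lens subluxation and stable visual conditions will be included in the non-surgical group", and "Patients with severe lens subluxation who accept CEL surgery will be included in the surgical group".

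The Introduction reports two thresholds from earlier work. One study "recommended surgical intervention when the near vision of children was worse than 0.4 in LogMAR acuity". Other researchers held that "surgery should be performed when the best-corrected visual acuity (BCVA) is less than 0.3 or monocular diplopia occurs", with no scale named. The Objective section says the results should serve as a reference "specifically for choice of surgical timing and surgical method".

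**The concern.** LogMAR rises as vision falls. A criterion of below 0.3 on that scale therefore picks out the better-seeing eyes, the opposite of what an acuity indication for lens surgery should do. It also sits badly with the abstract: a patient with mild, stable subluxation and 20/20 corrected vision belongs in the non-surgical group, yet meets this indication for surgery.

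The line is an operative threshold for intraocular surgery in a cohort that enrols from age 3. It also bears on when a conservatively managed patient converts to surgery. Change in BCVA is part of the primary outcome, so the threshold shapes the preoperative BCVA of the surgical group.

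A reader can see that the line is wrong but cannot tell from the article which correction applies. The Introduction supports either one. Its first threshold is on the LogMAR scale with the right direction. Its second, 0.3 paired with monocular diplopia just as in the surgical list, makes sense only as decimal acuity.

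**Working it through.** **Inputs.** The threshold (0.3), its direction (below) and its scale (LogMAR) come from Preoperative management. The ETDRS LogMAR chart comes from Examinations. The article gives no acuity conversion of its own to reproduce.

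**Formulas.** By the definition of LogMAR, decimal acuity = 10^(−LogMAR), and the Snellen denominator = 20 × 10^(LogMAR).

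**Step 1: apply the criterion as written.**

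| LogMAR | Decimal | Snellen | Below 0.3? |
|---|---|---|---|
| 0.0 | 1.000 | 20/20 | yes |
| 0.1 | 0.794 | 20/25 | yes |
| 0.2 | 0.631 | 20/32 | yes |
| 0.3 | 0.501 | 20/39.9 | no |
| 0.4 | 0.398 | 20/50 | no |
| 0.6 | 0.251 | 20/80 | no |
| 1.0 | 0.100 | 20/200 | no |

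Every eye better than about 20/40 meets the criterion, and no worse eye does.

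**Step 2: the two plausible corrections.**

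- Sign wrong: LogMAR above 0.3. Decimal = 10^(−0.3) = 0.50; Snellen = 20 × 10^0.3 = 39.9, so worse than about 20/40.
- Scale label wrong: decimal below 0.3. LogMAR = −log10(0.3) = 0.5229; Snellen = 20/0.3 = 66.7, so worse than about 20/67.

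**Step 3: the gap between them.** 0.5229 − 0.3 = 0.2229 LogMAR. Assuming the usual ETDRS scoring of 0.1 LogMAR per line and 0.02 per letter, that is 0.2229/0.1 = 2.2 lines, or 0.2229/0.02 = 11.1 letters. An eye between 0.30 and 0.52 LogMAR meets the acuity criterion under the first correction and not under the second.

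**Step 4: what does not change.** The sample size rests on a 15% complication incidence, a 20% relative margin and 10% loss. It does not use the acuity threshold, so it is the same under either correction.

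**The case against.** The strongest reply is that no clinician would operate on a 20/20 eye because of a misprinted sign. The other three criteria all rest on symptoms or pathology, the abstract reserves surgery for severe subluxation in patients who accept it, and one surgeon operates on every case. The abstract gives no acuity cut-off, so the conflict with it is indirect. Preoperative BCVA is recorded, so timing relative to acuity can be examined later whatever cut-off was used. The analysis section does not use the threshold either. Finally, the article names LogMAR both in the criterion and for the chart, so the natural repair may be simply to reverse the symbol. The decimal reading leans on a threshold credited to other researchers, and the surgical list cites a different source.

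Much of this stands. The line is a wording error rather than a deliberate design choice, harm to patients is not shown, and the 0.22 LogMAR gap is a distance between two candidate corrections, not a measured effect. The flow chart, case report form and full protocol are not visible and may state the threshold correctly or repeat the slip.

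None of it makes the printed criterion right. Common sense rules out the literal reading but does not choose between above 0.3 and above 0.52. Poor-acuity eyes may still qualify through the other three criteria, but not through the one written for them.

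**Conclusion.** The criterion is wrong as written and must be corrected. On the chart the study uses, it is met by eyes better than about 20/40 and not by worse ones. That conclusion rests only on the definition of LogMAR and the printed text. The size of the remaining ambiguity, 0.22 LogMAR or about 11 letters, is conditional on the two corrections considered here and on standard ETDRS scoring. How many patients fall between the two thresholds cannot be computed, because the article gives no baseline BCVA distribution. The conclusion is confined to the first surgical criterion; it does not claim that any patient has been assigned to the wrong group.

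**What to change.** Restate the first criterion in LogMAR, in the right direction, with the Snellen equivalent beside it. Depending on what the investigators confirm, it should read either:

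- BCVA worse than 0.3 LogMAR (above 0.3, about 20/40), if the sign was wrong; or
- BCVA worse than 0.52 LogMAR (above 0.52, about 20/67), if decimal 0.3 was intended.

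Use the same wording in the case report form and the group-assignment rule, and in Figure 1 if it repeats the criterion. The cost is a one-line protocol correction and a check of the form; sample size and visit schedule are unaffected.

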#### Secondary outcomes

Change of axial length (time frame: non-surgical group is evaluated at the first visit and 1, 2, 3 years after enrolment; surgical group is evaluated at preoperation, 3 months, and 1, 2, 3 years postoperatively).High-order aberrations (time frame: non-surgical group is evaluated at the first visit and 1, 2, 3 years after enrolment; surgical group is evaluated at preoperation, 3 months, and 1, 2, 3 years postoperatively).Central cornea endothelial cell loss (time frame: preoperation, 3 months, and 1, 2, 3 years postoperatively).The state of zonules (time frame: non-surgical group is assessed at the first visit and 1, 2, 3 years after enrolment; surgical group will be assessed preoperatively).Anterior chamber angle (time frame: non-surgical group is assessed at the first visit and 1, 2, 3 years after enrolment; surgical group will be assessed preoperatively, 3 months, and 1, 2, 3 years postoperatively).Tilt and eccentricity of IOL (time frame: 3 months, and 1, 2, 3 years postoperatively).IOP (time frame: non-surgical group is evaluated at the first visit and 1, 2, 3 years after enrolment; surgical group is evaluated at preoperation, 3 months, and 1, 2, 3 years postoperatively).Aortic root diameter (time frame: non-surgical group is evaluated at the first visit and 1, 2, 3 years after enrolment; surgical group is evaluated at preoperation and 1, 2, 3 years postoperatively).Aortic root (sinuses of Valsalva) Z-score, adjusted by body surface area (Z-score) (time frame: non-surgical group is evaluated at the first visit and 1, 2, 3 years after enrolment; surgical group is evaluated at preoperation and 1, 2, 3 years postoperatively).Incidence of valvular heart disease (time frame: non-surgical group is evaluated at the first visit and 1, 2, 3 years after enrolment; surgical group is evaluated at preoperation and 1, 2, 3 years postoperatively).Body mass index (BMI) (time frame: non-surgical group is evaluated at the first visit and 1, 2, 3 years after enrolment; surgical group is evaluated at preoperation and 1, 2, 3 years postoperatively).Metacarpophalangeal joint length (time frame: non-surgical group is evaluated at the first visit and 1, 2, 3 years after enrolment; surgical group is evaluated at preoperation and 1, 2, 3 years postoperatively).Choroidal thickness (time frame: non-surgical group is evaluated at the first visit and 3 years after enrolment; surgical group is evaluated at preoperation and 3 years postoperatively).Choriocapillaris flow deficits (time frame: non-surgical group is evaluated at the first visit and 3 years after enrolment; surgical group is evaluated at preoperation and 3 years postoperatively).Genetic mutation state of patients (time frame: preoperation).Vision-related quality of life (time frame: non-surgical group is evaluated at the first visit and 3 years after enrolment; surgical group is evaluated at preoperation and 3 years postoperatively).

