### Statistical analysis plan

Statistical analysis will be performed using Stata V.15.0 (StataCorp, College Station, Texas, USA). Quantitative data conforming to a normal distribution will be described as the mean±SD. The difference between the baseline and follow-up data will be compared by one-way analysis of variance. The median±IQR will describe the quantitative data of the skewness distribution. The Wilcoxon signed-rank test will be used to compare these data’s differences. For qualitative data described as proportions, the Χ^2^ test or Fisher’s exact test will be used to compare the differences between groups. P<0.05 is considered statistically significant. The differences and 95% CI in the changes of BCVA and other parameters will be calculated. The univariable linear regression model will estimate these changes and their associated factors. All variables with p<0.05 in the univariable regression analysis will be included in the multivariable linear regression model.

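### The surgical group combines eyes operated on for an existing complication with eyes operated on for acuity, diplopia or progression; change from the preoperative value then mixes different effects, and for IOP a rise can be offset

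*Protocol article*

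**What the plan says.** All of this is in the protocol article.

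- **Reasons for surgery (Preoperative management).** Any one of four is enough. Reasons 1 to 3 are an acuity criterion, monocular diplopia, and subluxation that progresses to affect the pupillary axis. Reason 4 is an eye "complicated with severe cataract or secondary glaucoma or corneal endothelial decompensation or retinal detachment".
- **Group (abstract, Methods and analysis).** "Patients with severe lens subluxation who accept CEL surgery will be included in the surgical group". Surgery methods management divides operations by zonular extent, not by indication.
- **Outcomes.** "The primary outcome is the change of BCVA and the incidence of complications", with the surgical group assessed from a preoperative baseline to 3 years. IOP is a secondary outcome on the same schedule. So is "Central cornea endothelial cell loss (time frame: preoperation, 3 months, and 1, 2, 3 years postoperatively".
- **Analysis (Statistical analysis plan).** "The difference between the baseline and follow-up data will be compared by one-way analysis of variance". Univariable linear regressions follow, and variables with p<0.05 go into the multivariable model. That is the only stated route into the model, and no candidate variables are listed.
- **Purpose (Objective).** The study is to serve as a reference for management, "specifically for choice of surgical timing and surgical method".

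**The concern.** A change score describes the effect of an operation only if the starting value is not itself the reason for operating. Under reason 4 it can be. Secondary glaucoma is an indication and also determines the preoperative IOP. Endothelial decompensation is an indication and also determines the preoperative cell count. Cataract and retinal detachment are indications and also lower the preoperative acuity. In these eyes the change partly measures what happens to the complication; in the remaining eyes it measures what the operation does to an eye without that complication.

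Two things are at stake. First, a pooled mean may describe neither kind of eye, and for IOP a fall in one part can cancel a rise in the other. The protocol expects raised pressure after surgery, since Postoperative management sets steps for IOP above 25 and above 40 mm Hg. Second, operating before or after a complication has appeared is a contrast in timing, which the objective asks about, and no stated analysis supplies it.

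**Working it through.** **Figures in the article.** None bears on this point: it gives no share of operated eyes by indication and no expected change in IOP, cell count or BCVA. Its one calculation, the sample size, does reproduce (1.96² × 0.15 × 0.85 / 0.03² = 544.2; 544/0.9 = 604.4) but does not affect the argument. Every input below is an assumption.

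**Formula.** Let w be the share of operated eyes with secondary glaucoma as an indication, d their mean change and u the mean change in all other operated eyes. Then

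pooled mean change = w × d + (1 − w) × u,

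which is zero when w = u / (u − d).

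**IOP, with u = +1.5 mm Hg:**

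| Glaucoma share w | d = −10 | d = −15 | d = −20 |
|---|---|---|---|
| 5% | +0.925 | +0.675 | +0.425 |
| 10% | +0.35 | −0.15 | −0.65 |
| 15% | −0.225 | −0.975 | −1.725 |

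Example: 0.10 × (−10) + 0.90 × 1.5 = −1.00 + 1.35 = +0.35. At 5% the pooled mean is still a rise throughout. At 10% its sign depends on d. At 15% it is a fall throughout. The rise cancels exactly at 1.5/11.5 = 13.0%, 1.5/16.5 = 9.1% and 1.5/21.5 = 7.0%.

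**IOP, other assumptions.** With u = +2 and d = −12, the pooled mean is +1.3, +0.6, −0.1 and −0.8 mm Hg at shares of 5%, 10%, 15% and 20%, and it is zero at 2/14 = 14.3%. For rises of 1 to 3 and falls of 8 to 15 mm Hg, the cancelling share runs from 1/16 = 6% to 3/11 = 27%.

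**Endothelial cell loss.** Assume a 10% loss in other eyes and 3% in eyes that start depleted. The pooled change is −9.65% at a 5% share (0.95 × −10 + 0.05 × −3) and −8.6% at 20%. The loss is understated but keeps its sign.

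**BCVA.** Assume both parts improve, by −0.2 and −0.6 LogMAR. The pooled mean is −0.22 at a 5% share and −0.28 at 20%. It moves with case mix and does not cancel. The sign changes only if the other eyes are assumed to get worse: +0.05 against −0.6 gives about +0.018 at 5% and −0.015 at 10%.

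**Could the stated regression recover the difference?** Only if indication is offered as a candidate and reaches p<0.05 on its own. A small reason-4 stratum may not. For IOP, a single indicator for reason 4 also puts glaucoma eyes together with cataract and detachment eyes, which weakens the contrast.

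**The case against.** The strongest case against runs as follows.

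- **The point rests on silence.** The statistical section never says that operated eyes are analysed only as a whole, the associated factors are left open, and subgroup and covariate lists usually belong in a fuller plan. The case report form is not shown and may already record the indication. This stands in part: the article does not show that the information is lost. It does, however, fix the group, the baseline and the covariate entry rule, and that rule can drop indication even when it matters.
- **Harm is not read from means alone.** Incidence of complications is a primary outcome, and complications are collected at every visit. This stands. A reader might infer that pooling hides harm; the documents do not support that. What remains open is whether a complication present before surgery counts as incident.
- **Eligibility narrows the mix.** The exclusion reads "Combined with other ophthalmic diseases such as primary glaucoma, uveitis and corneal disease". It may keep decompensated corneas out at enrolment. It does not name secondary glaucoma, cataract or retinal detachment, and it does not cover decompensation that develops after enrolment. The article should say how this exclusion and the fourth reason fit together.
- **The reasons overlap.** An eye with severe cataract may also meet the acuity criterion. This stands, so any split needs an assignment rule.
- **Glaucoma alone may not reach 10% to 15% of operated eyes.** This is possible; the documents do not say.

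**Conclusion.** The point holds in a limited form and should be acted on. The article allows surgery because of a complication, measures operated patients from a preoperative baseline as one group, and states no analysis by indication. Pooled changes will therefore mix different effects, and the before-or-after-complication contrast relevant to the timing aim is not provided.

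The consequence differs by outcome. For IOP, opposite directions are plausible: on the assumed values, a mean rise of 1.5 mm Hg in the other eyes is reduced at a 5% glaucoma share, roughly cancelled at about 7% to 13%, and reversed at 15%. For endothelial loss the expected result is dilution with the same sign. For BCVA it is dependence on case mix.

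A reader might infer that all three outcomes mix opposite effects. The documents do not support this for endothelial loss or for BCVA, where reversal needs the other eyes to worsen. Nor do they support a firm size even for IOP, because shares and changes are all assumed. A reader might also infer that eyes without a complication should become the main estimate of the effect of surgery. That would change the target population, and nothing in the objective requires it.

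**What to change.** 1. **Record.** Add to the case report form, for each operated eye, every listed reason for surgery present at the time of operation. Class an eye under reason 4 if any of the listed complications is present, whatever else applies.
2. **Report.** Keep the overall summary of the surgical group. Beside it, give BCVA change, IOP, endothelial cell loss and complications separately for eyes with reasons 1 to 3 only and for eyes with reason 4. Show IOP separately for eyes with secondary glaucoma.
3. **Model.** Enter indication in the multivariable models whatever its univariable p-value.
4. **Count.** State that only complications absent before surgery are counted as incident after it.

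The cost is one set of tick boxes that the surgeon can complete at the time, and a few sentences in the Statistical analysis plan section. The drawback is that the reason-4 stratum may be small, with wide intervals, so its results would be descriptive. No surgical indication changes.
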